## Abstract

**Introduction:**

Hip fracture is a serious injury in adults, especially those aged over 60 years. The most common type of hip fracture (displaced intracapsular) is treated for the majority of patients with a partial hip replacement (hemiarthroplasty). The hemiarthroplasty implant can be fixed to the bone with or without bone cement. Cement is the current recommended technique but recently some risks have been identified, which could potentially be avoided by using uncemented implants. Controversy, therefore, remains about which type of hemiarthroplasty offers patients the best outcomes.

This is the protocol for a multicentre randomised controlled trial comparing cemented hemiarthroplasty versus uncemented hemiarthroplasty for patients 60 years and over with a displaced intracapsular hip fracture.

**Methods and analysis:**

Multicentre (a minimum of seven UK hospitals), multisurgeon, parallel group, two-arm, superiority, randomised controlled trial. Patients aged 60 years and older with a displaced intracapsular hip fracture treated with hemiarthroplasty surgery are eligible. Participants will be randomly allocated on a 1:1 basis to either a cemented hemiarthroplasty or a modern hydroxyapatite coated uncemented hemiarthroplasty. Otherwise all care will be in accordance with the National Institute for Health and Care Excellence guidance. A minimum of 1128 patients will be recruited to obtain 90% power to detect a 0.075-point difference in the primary endpoint: health-related quality of life (EuroQol 5 dimensions 5 levels) at 4 months postinjury. The treatment effect will be estimated using a two-sided t-test adjusted for age, gender and cognitive impairment based on an intention-to-treat analysis. Secondary outcomes include mortality, complications including revision surgery and cause, mobility status, residential status, health-related quality of life at 1 and 12 months and health resource use. A within-trial economic analysis will be conducted.

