The stratification used for randomisation will ensure balance in treatment allocation across recruitment centres. In addition to the unadjusted analyses, we will also undertake regression analyses to adjust for any imbalance between treatment groups in patient baseline (preinjury) EQ-5D, age and gender. Age and gender are likely to be reported by all study participants, however, if baseline EQ-5D is poorly reported, such that it reduces the available sample size for the definitive analysis, then it will not be included in the definitive model. The fixed-effects analysis (linear regression model) will be generalised by adding a random effect for recruitment centre to allow for possible heterogeneity in patient outcomes due more generally to the recruitment centre. The adjusted mixed-effects regression will be the definitive (primary) analyses and will be reported as such. Analyses will be undertaken using the specialist mixed-effects modelling functions available in the software package R (http://www.r-project.org/).^17^ EQ-5D data will be assumed to be approximately normally distributed; possibly after appropriate variance-stabilising transformation. The primary focus will be the comparison of the two treatment groups of patients, and this will be reflected in the analysis which will be reported together with appropriate diagnostic plots that check the underlying model assumptions. Results will be presented as mean differences between the trial groups, with 95% CIs. The primary analysis will be on an ITT basis. However, a per-protocol analysis will also be undertaken by repeating the primary outcome analysis using the actual treatment received by participants (in contrast to the allocated treatment) as a sensitivity analysis to examine the robustness of conclusions to different assumptions about departures from the stated protocol.

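### The abstract and the Statistical analysis section name different primary analyses, and the definitive model leaves one covariate and the outcome scale open

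*Protocol article*

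**What the plan says.** **Abstract, Methods and analysis.** "The treatment effect will be estimated using a two-sided t-test adjusted for age, gender and cognitive impairment based on an intention-to-treat analysis". Neither baseline EQ-5D nor recruitment centre is mentioned.

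**Statistical analysis section.** An unadjusted linear regression comes first and is called initial. It is followed by "regression analyses to adjust for any imbalance between treatment groups in patient baseline (preinjury) EQ-5D, age and gender". The model is then extended by "adding a random effect for recruitment centre to allow for possible heterogeneity in patient outcomes". The section states which result counts: "The adjusted mixed-effects regression will be the definitive (primary) analyses and will be reported as such". Cognitive impairment is not in this covariate list.

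The same section leaves two choices conditional:

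- Baseline EQ-5D: "if baseline EQ-5D is poorly reported, such that it reduces the available sample size for the definitive analysis, then it will not be included". No threshold is given.
- Outcome scale: EQ-5D is treated as roughly normal, "possibly after appropriate variance-stabilising transformation". No transformation is named and no trigger is given, yet results are promised as mean differences with 95% confidence intervals.

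The section also scores death as zero on EQ-5D in all analyses and bases the main analysis on complete cases. The Sample size section powers the trial on a difference of 0.075 index points.

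**The concern.** Two current statements in one document describe the primary analysis differently, so this is not detail left to an analysis plan. Someone checking the trial report against the protocol could cite either covariate list as the pre-specified one.

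The covariate in dispute matters in this population. Patients with and without capacity are eligible, their inclusion is listed as a strength, and incapacity is one of the main reasons given for expecting only 60% of participants to be available at 4 months. Whether a complete-case primary model conditions on cognitive status is therefore a substantive choice. It also carries over: the repeated-measures model takes its fixed effects from the primary analysis, and the secondary continuous outcomes follow the same strategy.

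The transformation clause raises a separate question. A treatment difference on a transformed scale answers a different question from the one the trial was sized for, and the decision to transform could be taken after the data are seen.

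**Working it through.** **1. The two statements side by side**

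| Element | Abstract | Statistical analysis section |
|---|---|---|
| Method | t-test, described as adjusted | mixed-effects linear regression |
| Age, gender | yes | yes |
| Cognitive impairment | yes | no |
| Baseline EQ-5D | no | yes, unless poorly reported |
| Centre | no | random effect |
| Outcome scale | not stated | index, possibly transformed |

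**2. The stated sample size.** Inputs from the Sample size section: difference 0.075, two-sided alpha 0.05, power 90%, 60% available. With SD 0.30, an unadjusted two-sample t-test needs 337.2 per group, rounded up to 338. Then 338/0.6 = 563.3, rounded up to 564, and 2 × 564 = 1128. The plan's figure reproduces and depends on neither covariate list.

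**3. Each model on its own.** In 4000 simulated null trials of 676 patients (assumed covariate effects, centre effect left out), the abstract's covariates and the body's covariates with and without baseline EQ-5D each rejected in 4.3% to 4.8%. No single specification is invalid.

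**4. Choosing between the two lists after seeing the data.** Let rb and rc be the shares of outcome variance explained by baseline EQ-5D and by cognitive status. The documents give neither, so both are assumed, and the two covariates are taken as uncorrelated. Under the null, the correlation between the two test statistics is

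ρ = (1 − rb − rc) / √[(1 − rb)(1 − rc)]

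The chance that at least one exceeds 1.96 in absolute value comes from the bivariate normal distribution:

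| rb | rc | ρ | at least one significant |
|---|---|---|---|
| 0.10 | 0.05 | 0.85/√(0.90 × 0.95) = 0.919 | 6.8% |
| 0.16 | 0.10 | 0.74/√(0.84 × 0.90) = 0.851 | 7.5% |
| 0.25 | 0.15 | 0.60/√(0.75 × 0.85) = 0.751 | 8.1% |

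The simulation in step 3 gives 7.8% for the smallest p value among its three covariate sets, and 8.4% when one transformed-outcome version is added.

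**5. What adding cognitive status to the body's model would gain.** Power = Φ(0.075/SE − 1.96), with SE = SD × √(1 − R²) × √(2/338), where R² is rb for the body's model and rb + rc once cognition is added. At SD 0.30, the value behind Table 1:

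| rb, rc | body's model | with cognition added |
|---|---|---|
| 0.10, 0.05 | 92.9% | 94.1% |
| 0.16, 0.10 | 94.4% | 96.6% |
| 0.25, 0.15 | 96.4% | 98.7% |

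The gain is 1.3 to 2.4 percentage points: useful, but small.

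**6. The open choices in the body's model.** In a complete-case analysis, any missing baseline value reduces the available sample. Read literally, one missing value would remove the covariate; read loosely, the decision is a judgement. On the scale, deaths score exactly zero, so a plain log is undefined for every death. More generally, a difference on any non-linear scale cannot be set against 0.075 index points.

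**The case against.** The strongest reply is that the body settles the matter. It names the adjusted mixed-effects regression as definitive and ranks the unadjusted regression as initial, and an abstract is only a condensed account. This stands as far as model class and primacy go. A reader might infer that the primary test is not fixed at all, and the document does not support that.

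It can also be said that an adjusted t-test is loose shorthand, because the test of a treatment coefficient in a regression is a t-test. That is fair for the method. It does not explain a covariate that is missing from the body's list, or the absence of baseline EQ-5D and centre from the abstract.

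A reader might also infer that the trial runs a false-positive rate of 7% to 9%. It does not. The upper part of that range comes from adding the unadjusted model, which the protocol ranks below the definitive one, and any inflation needs a free choice of the smallest p value after seeing the data. Nor does leaving out cognition cost the trial the gap from about 84% power to 86–89%. That comparison sets cognition against an unadjusted model at SD 0.33, whereas the body's model already contains baseline EQ-5D. The two SD values in the Sample size section are a separate matter.

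Finally, the criterion for a contingent transformation is often left to an analysis plan, which is not shown here. That is accepted for the criterion. The clause still conflicts with the mean differences promised in the same section. Negative index values are not needed for this point, and the article does not mention them.

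**Conclusion.** The point holds as a contradiction to be reconciled, and it should be fixed. It does not invalidate the trial. The two parts of the article disagree on cognitive impairment, baseline EQ-5D and centre. Within the definitive model, retention of baseline EQ-5D and the outcome scale are left to unspecified judgement.

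Either covariate list, fixed in advance, gives a valid test at about 5%. The rate of about 7% to 8% applies only to a choice between the two lists made after seeing the data. It rests on assumed explained variance of 10–25% for baseline EQ-5D and 5–15% for cognition, uncorrelated covariates and a normal approximation. The power gain of 1.3 to 2.4 points at SD 0.30 rests on the same assumptions. The contradiction itself and the mismatch of scale need no assumption.

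**What to change.** State the same primary model in the abstract and in the Statistical analysis section:

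- **Outcome:** untransformed, death-adjusted EQ-5D index at 4 months.
- **Model:** linear mixed model with fixed effects for treatment, age, gender, cognitive impairment and baseline EQ-5D, and a random effect for recruitment centre.
- **Missing baseline EQ-5D:** a rule fixed before unblinding, for example imputation of the missing baseline covariate, so that including it removes no patients. This replaces the open-ended condition on poor reporting.
- **Abstract:** replace the t-test wording with this model.
- **Transformation:** sensitivity analysis only.

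The cost is a change of wording, one more covariate than the body now lists, and a pre-specified rule for missing baseline values. Making baseline EQ-5D mandatory without that rule would be worse than the present text, because the complete-case analysis could then lose patients. The sample size is unaffected.

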**Ethics, dissemination and funding:**

Wales Research Ethics Committee 5 approved the feasibility phase on 2 December 2016 (16/WA/0351) and the definitive trial on 22 November 2017 (17/WA/0383). This study is sponsored by the University of Oxford and funded by the National Institute for Health Research, Research for Patient Benefit (PB-PG-0215–36043 and PB-PG-1216–20021). A manuscript for a peer-reviewed journal will be prepared and the results shared with patients via local mechanisms at participating centres.

**Trial registration number:**

ISRCTN18393176

Strengths and limitations of this studyPragmatic multicentre randomised controlled trial.Powered to detect differences in health-related quality of life.Inclusion of participants with and without cognitive impairment.Outcomes include the UK core outcome set for hip fracture.The trial will not capture late complications, implant failure or revision surgery beyond 1-year postinjury.

## Introduction

Hip fracture is one of the biggest challenges facing patients and healthcare systems. Every year, in the UK, there are more than 65 000 hip fractures.^1^ Displaced ‘intracapsular’ fractures represent approximately half of all hip fractures. In these fractures, the head of the femur is broken off at the neck. The blood supply to the femoral head is tenuous and, even if the fracture is fixed back in to its anatomical position, fracture healing is unreliable and 40% of patients will have a failure of fixation. For this reason, arthroplasty (replacement) of the femoral head is preferred in the UK. A minority of patients receive a ‘total hip arthroplasty’ (replacing the ‘socket’ of the hip joint as well as the femoral head) if they are particularly active before the fracture, but, in the most cases, only the head of the femur is replaced; a hemiarthroplasty.

The National Institute for Health and Care Excellence (NICE)^2^ guidelines for hip fracture recommend the use of bone cement to aid in the fixation of the hemiarthroplasty implant to the bone. These guidelines are based on outcomes of studies, which show less postoperative pain and better function when cemented components were used compared with their first generation uncemented counterparts (eg, the Austin Moore prosthesis). The evidence base for these guidelines is summarised in a Cochrane review,^3^ which acknowledged the lack of evidence for more contemporary uncemented implants and concluded that ‘there is still a place for trials of contemporary uncemented stems with cemented stem hemiarthroplasty’. A recent independent systematic review and meta-analysis compared cemented hemiarthroplasty with modern uncemented hemiarthroplasty and concluded: ‘there remains a need for a methodologically sound, large muticentre RCT comparing modern cemented and cementless hemiarthroplasty stems in the medium—and long-term, not only focusing on mortality and complications but also on patient reported outcome measures*.’*
4

This is the protocol for a multicentre parallel-group randomised controlled trial that compares cemented hemiarthroplasty and modern hydroxyapatite coated uncemented hemiarthroplasty.

## Aims and objectives

The aim of this randomised controlled trial is to compare health-related quality of life (HRQoL) in participants over 60 years of age with a displaced intracapsular hip fracture receiving a modern hydroxyapatite coated uncemented hemiarthroplasty versus the current standard-of-care cemented hemiarthroplasty.

### The primary objective is

To quantify and draw inferences on observed differences in participants’ HRQoL between the trial treatment groups at 4 months postinjury.

### The secondary objectives are

To quantify and draw inferences on the observed differences in participants’ HRQoL between the trial treatment groups at 1 and 12 months postinjury.To quantify and draw inferences on the observed differences in the proportion of complications, including further surgery, within the first 12 months postinjury between the trial treatment groups.To quantify and draw inferences on observed differences in mortality, mobility and residential status at 1, 4 and 12 months postinjury.To investigate, using appropriate statistical and economic analytical methods, the resource use, costs and incremental cost effectiveness of the trial treatment groups at 4 months postinjury.

## Methods and analysis

### Study design

A multicentre, parallel group, two-arm, superiority, standard-of-care randomised controlled superiority trial in a minimum of seven UK recruitment centres. Each of these recruitment centres is recruiting hip fracture patients as part of the World Hip Trauma Evaluation hip fracture cohort study.^5^ The study is conducted in two phases: an initial feasibility phase in which the acceptability of the interventions and trial processes were tested, and a definitive phase which comprises the main trial. Data from the feasibility phase will be locked, and not analysed, at completion. At the end of the definitive main trial phase, data from the two phases will be analysed together as a single dataset.

### Patient and public involvement

At the centre of this work is the potential for patient benefit by reducing the risks of hip fracture surgery and improving patient outcomes. The involvement of patient and public representatives has, therefore, been a key element of this work to ensure that the running of the trial remains patient focused. JG and AM are patient representative coauthors who have been involved in all aspects of this work from designing the trial, obtaining grant funding, developing the trial materials and participation in the running of the trial. More specifically, the role of patient representatives has been to ensure that trial processes and information are focused on patients, to provide the patient perspective as members of the trial management group, and to ensure that all trial processes have taken into account the needs of patients both with and without cognitive impairment.

### Eligibility

Patients will be screened against the following criteria:

#### Inclusion criteria

All patients, both those with and without capacity, presenting with a displaced intracapsular fracture of the hip suitable for hemiarthroplasty.

#### Exclusion criteria

Patients younger than 60 years of age.Patients who are managed non-operatively.Patients who are treated with a total hip replacement.

### Consent

Patients with a hip fracture are a clinical priority for urgent operative care. They undergo surgery on the next available trauma operating list. All patients with a fracture of the hip are in pain and will have received opiate analgesia. It is, therefore, understandable that the majority of patients find the initial period of their treatment in hospital confusing and disorientating. Similarly, patients’ next of kin, carers and friends are often anxious at this time and may have difficulty in absorbing the large amounts of information that they are given about the injury and plan for treatment. In this emergency situation, the focus is on obtaining consent for surgery (where possible) and on informing the patient and any next of kin about immediate clinical care. It is often not possible for the patient, relative or carer (consultee) to review trial documentation, consider the information and communicate an informed decision about whether they would wish to participate in the study. The consent procedure for this trial will reflect that of the surgery, with the clinical team assessing capacity before taking consent for the surgical procedure, and this capacity assessment then being used to guide the proper approach to consenting to the research. An appropriate method, in line with the mental capacity act and approved by the National Research Ethics Committee, will be used to gain either prospective or retrospective consent from the patient or appropriate consultee by a Good Clinical Practice (GCP) trained, appropriately delegated member of the research team.

### Randomisation and blinding

The allocation sequence will be computer generated by the trial statistician and administered, using secure online randomisation, by Oxford Clinical Trials Research Unit (OCTRU), University of Oxford. Participants will be enrolled by the operating surgeon or trial research associate. The research associate will receive notification of the allocated treatment and inform the surgeon and the operating theatre staff. The randomisation algorithm will use variable block sizes (2, 4 and 6), to ensure good treatment balance, at each of the recruitment centres. The surgery will be performed under the care of the consultant surgeon on-call at the time the patient is admitted as per local practice in the recruitment centres. The large number of surgeons—previous experience in similar trials suggests over 200 surgeons will take part—and the wide skill mix should minimise any surgeon-specific effects such that stratification by surgeon is unnecessary. In order to negate bias in the self-reported HRQoL outcome measures, participants will be blinded to treatment allocation. The operating surgeon cannot be blinded to the allocation but they will not be involved in the assessment of outcomes. Patients will be blinded until the completion of the trial when the blinding will be broken if requested by the patients. There will be no formal analysis of the success of the blinding.

### Postrandomisation withdrawals and exclusion

Throughout the study, screening logs will be kept to determine the number of patients assessed for eligibility and reasons for any exclusion. Participants may withdraw from the study at any time without prejudice. If a participant withdraws from the study completely, data collected up until the point of withdrawal will be included in the final analysis. Patients who decline to continue to take part will be given the opportunity to discuss and inform the research team of the reasoning behind their decision not to take part. Similarly, data obtained from participants who die before they or a personal consultee has been approached about continued consent/agreement will be included in the final analysis.

### Treatments

#### Standardised treatment pathway

Participants will usually be assessed in the emergency department. Diagnosis of a hip fracture will be confirmed by a plain radiograph, as per routine clinical care. Supplementary imaging will be at the discretion of the treating clinical team. Routine investigations, anaesthetic assessment, antibiotic and venous thromboembolic prophylaxis will be used as per local policy. A regional or general anaesthesia technique will be used for every participant as per routine clinical care. All participants will receive perioperative prophylactic antibiotics in accordance with current protocols agreed at each recruitment centre. Postoperative analgesia will be prescribed intraoperatively and reviewed by the responsible clinical teams as appropriate.

In the postoperative period, as per standard of care, all participants will undergo a physiotherapy and occupational therapy assessment to create a rehabilitation plan. The aim of this plan will be for participants to mobilise through early, active and full weight bearing. Participants will be discharged from the acute Orthopaedic Trauma Ward at the earliest safe opportunity to the most appropriate discharge destination as determined by the multidisciplinary clinical team. Participants will be given the relevant National Health Service (NHS) Trust information packs.

